### **7.1.7 Premature termination of the study**

The sponsor has the right to close this study at any time. The IEC and the competent regulatory authority must be informed within 15 days of early termination.

The trial or single dose steps will be terminated prematurely in the following cases:

- If adverse events occur which are so serious that the risk-benefit ratio is not acceptable.
- If the number of dropouts is so high that proper completion of the trial cannot realistically be expected.

## **8. METHODOLOGY**

At the department of the Medical University of Vienna patients routinely receive intratympanic application of triamcinolone acetonide.

1 mL suspension containing 10mg (Groups 1 and 3) or 40mg (Groups 2 and 4) of triamcinolone acetonide is applied intratympanically via a 25G (0.50x90mm, 3.50 IN) needle after local anesthesia with xylocaine spray (10mg/Puff).

During the cochlear implant surgery, the cochlea is entered mostly via round window approach. Alternatively, if the round window cannot be identified, a cochleostomy is performed. After entering the cochlea, about 20µL of perilymph are sampled using a sterile disposable aspirator with a diameter of 0.4mm. A sterile insulin syringe is used to aspirate the perilymph. The perilymph sampling method has been performed similarly in other studies [2, 10].

Simultaneously a blood sample of 4ml is drawn in a heparin blood tube with a standard butterfly needle.

The sample of perilymph is stored in an eppendorf vial (volume 0,2ml) and frozen to approx. -80°.

The blood sample is centrifuged at 3000g, 20°C for 3 minutes at. The plasma is removed and stored in eppendorf vials (volume 2ml) and also frozen to approx.-80°. Both vials will be labeled with the patient number. Patients will be numbered with a randomly assigned three-digit number.

#### *Quantification of Triamcinolone acetoneide*

Samples will be diluted with mobile phase consisting of acetonitrile/2 mM aqueous ammonium acetate (60:40) adjusted to pH 3.2 with formic acid [13] and stored at +4 ° C until analysis by high-performance liquid chromatography/mass spectrometry, comprising an Ultimate RSLC 3000 series System (Thermo Fisher Scientific, Vienna, Austria) and an API 4000 Triple Quadrupole Mass Spectrometer (AB Sciex instruments, Vienna, Austria) equipped with an electro- spray ionization ion source and controlled by the Analyst 1.5 software (Dionex, Vienna, Austria). The chromatographic separation of samples will be conducted by isocratic elution using an Acclaim® 120 C18 reversed-phase LC column (2.1 × 150 mm, 3 µm; Thermo Fisher Scientific, Vienna, Austria) at 25 ° C. The run time will be 15 min at a flow rate of 0.5 ml/min, and the retention time of TAAc is about 1.28 min. Released TAAc will be selectively detected and quantified by tandem mass spectrometry fragmentation giving a quasimolecular ion at m/z 435 [M-H]+. Each sample series will be monitored by quality control samples containing certain amounts of TAAc within the range of the calibration graph.

[figure not shown]

### 8.1 Study medication

Active agent and characteristics: Triamcinolone acetonide

Trade name of the agent: Volon® A crystal suspension

Manufacturer: Mibe GmbH Arzneimittel

Drug supply: Dermapharm GmbH

Storage Instructions: Freezing is not allowed. Volon® A should be stored in the box to protect in from light.

Route of administration: Intratympanic

Information can be found in the investigator's brochure.

### **8.1.1 Dosage and administration**

Dose: 1mL of Volon® A 10mg or 40mg

Route of administration: intratympanic

Duration: single administration

### **8.1.2 Study-drug up- and down titration**

Not feasible

### **8.1.3 Study-drug delivery & drug storage conditions**

Triamcinolone acetonide is delivered at room temperature. The content has to be stored shielded from light, in the boxing. Triamcinolone acetonide should not be frozen.

It will be stored in the packaging at room temperature at the ENT department (ward 15J or 15I).

### **8.1.4 Study drug packaging and labeling**

Since Triamcinolone acetonide is a registered drug it will be stored in the original package.

### **8.1.5 IMP administration & handling**

1 mL Triamcinolone acetonide is applied intratympanically via a 25GA (0.50x90mm, 3.50 IN) needle after local anesthesia with Xylocaine spray (10mg/Puff).

Triamcinolone acetonide should be inspected before use. If agglomerations occur the drug should not be administered.

### **8.1.6 Drug Accountability**

The batch number will be documented on the Case Report Form. Triamcinolone acetonide will be administered at a single time point by a medical doctor intratympanically.

### **8.1.7 Procedures to assess subject's compliance**

Not applicable

### **8.1.8 Concomitant medication**

Allowed: All concomitant medication is allowed. Patients who have to take cortisone preoperatively will not be included in the study.

## **8.2 Randomization and stratification**

For Randomization <https://www.meduniwien.ac.at/randomizer> will be used. The first twenty patients will be randomized to the 40mg groups. The second half will be randomized to the 10mg groups. On day 0 participants will be randomized to one of 2 groups and the intratympanic application of triamcinolone will be administered accordingly on day 0 or day 1. Block randomization will be used in groups of 8. The method of permuted blocks randomization will be used with an equally weighted allocation to the 4 treatment groups (resulting in 10 patients per group).

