## 7. STUDY DESIGN

At the ENT department of the university hospital Vienna (AKH Wien) patients are treated with intratympanic triamcinolone acetonide before cochlea implantation to reduce inflammation and in some cases to protect residual hearing. Triamcinolone acetonide levels in cochlear perilymph will be evaluated in an open prospective clinical study. Patients scheduled for cochlear implant surgery between 18 and 90 years will be included. Patients who are treated with steroids preoperatively will be excluded from the study. Patients will be randomized after inclusion to one of four groups. The randomization is carried out to generate hypothesis for the needed dose and best time of application in the future. Triamcinolone acetonide will then be applied 20-24h before surgery or at the beginning of the surgery, depending on randomization (see below). About 20 µl of perilymph will be sampled simultaneously to a

blood sample during cochlear implant surgery. The first twenty patients will be randomized to Triamcinolone acetonide 40mg to allow for a first analysis of the samples. Patients 21 to forty will be randomized to Triamcinolone acetonide 10mg.

The probes will be stored at -80°C. Triamcinolone acetonide levels of the blood and perilymph will be determined by the pharmaceutical laboratory (Department of Pharmaceutical Technology and Biopharmaceutics, University of Vienna).

The patients will be randomized to 4 groups. Group 1 - Volon A® 10mg administration 20 - 24 hours before sampling. Group 2 – Volon® A 40mg administration 20 - 24 hours before sampling. Group 3 Volon® A 10mg – administration 1 to 2 hours before sampling. Group 4 – Volon A® 40mg administration 1 to 2 hours before sampling.

The time interval of application (1 to 2 hours and 20 to 24 hours before sampling) are a result of varying time of surgery depending on surgeons and patient anatomy as well as day to day clinical organization. Patients can withdraw consent at any time of the study.

The active phase of each patient will be between 6 and 9 days depending on time of follow-up visit.

[figure not shown]

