## **8.4 Benefit and risk assessment**

This study consists of a perilymph and a blood sample during cochlear implantation. Patients included in the study are deaf or profoundly hearing impaired. As previously shown in other studies sampling of the perilymph is a safe method.

This study can give us information on the absorption of Triamcinolone acetate by perilymph as well as information on the stability of Triamcinolone acetate after absorption of the perilymph. Since Triamcinolone acetate is used in the treatment of sudden SNHL and preoperatively, this study can deliver necessary information on the best timing of drug application and the necessary dose.

Additionally, a blood sample is taken, which can lead to known risks such as infections and hematoma.

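### Allocation text contradicts itself: dose follows enrolment order and only timing is randomised, so the descriptive dose comparison is confounded with enrolment period

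*Protocol*

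**What the plan says.** The protocol gives two descriptions of allocation.

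**Staged by dose.** Section 8.2 states: "The first twenty patients will be randomized to the 40mg groups. The second half will be randomized to the 10mg groups". Section 7 repeats the second half of the rule: "Patients 21 to forty will be randomized to Triamcinolone acetonide 10mg". It gives the reason for putting 40 mg first, which is to permit an early analysis of samples. Section 8.2 then says what is drawn at random: "On day 0 participants will be randomized to one of 2 groups", with the drug given on day 0 or day 1 accordingly. So the random element is the timing of application.

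**Randomised over four groups.** Section 7 also says that included patients are randomised among four groups. Section 8.2 specifies blocks of 8 and permuted-block randomisation "with an equally weighted allocation to the 4 treatment groups (resulting in 10 patients per group"). The synopsis (section 2) gives a 1:1:1:1 ratio for groups 1-4.

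**What the randomisation is for.** Section 7: "The randomization is carried out to generate hypothesis for the needed dose and best time of application in the future". Section 8.4 adds that "this study can deliver necessary information on the best timing of drug application and the necessary dose". The difference in levels between doses is a secondary objective (section 6). Section 11 analyses it descriptively, as hypothesis generating, with boxplots, medians and quartiles, and means with standard deviations of log concentrations.

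**The concern.** Whoever builds the list from section 8.2 has to choose between the two descriptions, because no list satisfies both. If the staged rule is followed, every 40 mg patient in groups 1-4 precedes every 10 mg patient, and the dose contrast compares two consecutive cohorts. The protocol nevertheless presents dose as something its randomisation informs, and the title calls the trial randomised. A reader of the results would take the 40 mg versus 10 mg boxplots as a comparison of concurrently randomised groups. Anything that changes between the two halves of a planned two-year recruitment would be read as an effect of dose.

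**Working it through.** **Inputs.** N = 40, 10 per group (sections 2 and 8.2); block size 8 (8.2); patients 1-20 at 40 mg and 21-40 at 10 mg (7 and 8.2); recruitment over two years (7.1.5). For the primary test: two-sided 5%, SD of paired log10 differences 0.81, difference 0.4, stated power 86% (section 11, sample size).

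**1. The plan's own power figure.** d = 0.4/0.81 = 0.494; noncentrality = 0.494 × √40 = 3.12; df = 39. The exact noncentral-t power is 86.1% (86.9% with d = 0.5). The stated 86% is reproduced. This test compares perilymph with blood within each patient, so the order of doses does not enter it. No power is stated for the dose comparison.

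**2. Four-group blocks against the staged rule.** An equally weighted block of 8 over four groups has 8/4 = 2 patients per group, hence 4 at 10 mg and 4 at 40 mg. The staged rule allows no 10 mg patient among the first twenty, so not even the first block can be used. Under concurrent allocation the same block fits exactly: 40/8 = 5 blocks, 5 × 2 = 10 per group.

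**3. Blocks of 8 over the two timing groups.** Each half has 20/8 = 2.5 blocks. Two full blocks give 8:8. The remaining four patients take half of a third block that holds four of each timing. The number k of one timing among these four has probability C(4,k)·C(4,4−k)/C(8,4), with C(8,4) = 70:

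- k = 2, split 10:10: 36/70 = 51%
- k = 1 or 3, split 9:11 or 11:9: 32/70 = 46%
- k = 0 or 4, split 8:12 or 12:8: 2/70 = 3%

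So 10 per group remains possible under staging, but it is not guaranteed unless the list is forced to balance.

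**4. Confounding of dose with period.** For patients 1-40, take a model with an intercept, dose, and first or second enrolment half. Dose and half are the same split of the patients, so the design matrix has rank 2 of 3 and the two effects cannot be estimated separately. If R is the true 40:10 ratio of raw concentrations and f is any multiplicative change between the halves (first relative to second), the observed ratio estimates R × f. The documents give no value for f. As a pure illustration, an assumed f of 1.5 to 2 would inflate the ratio 1.5- to 2-fold.

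**5. Would adjusting for a time trend help?** Only if drift is assumed to be linear. The correlation of dose with enrolment number is 0.866 in absolute value, so the variance of the dose effect is inflated by 1/(1 − 0.866²) = 4.0. A step between halves would remain inseparable.

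**The case against.** The strongest reply is that little depends on this contrast. Dose is one of the secondary objectives and is explicitly hypothesis generating, with no test, power or decision rule attached. The primary test is within patient, and timing remains randomised within each dose. Staging is deliberate and has a stated reason. All of this stands and limits the reach of the point. It does not remove the point: medians and boxplots carry a period effect in full, and the text still claims a randomisation for dose that the operative rule does not provide.

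Several stronger readings are tempting but not supported.

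- *Dose is confounded with assay batch.* Section 7 mentions only a first analysis of samples. It does not say that the 10 mg samples are run separately, or that 40 mg samples are not run again with them. Section 8 also requires quality control samples in each series, which would monitor calibration, though not sampling technique or patient mix.
- *Dose is confounded with surgical experience.* The protocol mentions surgeons only to explain the time windows.
- *Ten per group, or 1:1:1:1, is possible only with concurrent allocation.* It is not: staging can also give four groups of 10, with certainty if the list is balanced within each half.
- *Every dose summary is biased by drift.* A multiplicative change shared by plasma and perilymph cancels in the perilymph-to-blood ratio; the argument applies to raw concentrations.

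**Conclusion.** The allocation text in sections 7 and 8.2 is contradictory and cannot be implemented as written. Under the staged rule, dose is sequential and not randomised, and the 40 mg versus 10 mg comparison of raw concentrations is completely confounded with enrolment period. Candidate sources of a shift are patient mix, sampling technique and, if the stages are assayed separately, assay run. Whether any shift occurs, and how large it is, is unknown. The block size of 8 also does not fit a half of 20, so the 10:10 timing split is left to chance (51%) unless balance is forced.

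The damage is confined to a descriptive secondary objective and to the claims about dose in sections 7 and 8.4. A reader might infer that the main result is compromised; it is not, because the paired test keeps N = 40 and its 86% power. The randomised timing contrast within each dose is also intact.

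This conclusion takes patients 1-40 to be groups 1-4. Group 5 lies outside the 1:1:1:1 scheme, and its place in the sequence is not given.

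**What to change.** **If enrolment has not started:** replace the staged rule with one concurrent permuted-block list over groups 1-4, in blocks of 8 with 2 per group; five blocks give 10 per group. Do the early sample check on the first 20 patients. Those comprise two full blocks (8 at 40 mg) plus half of a third (0 to 4 more), so about 10 patients at 40 mg (8 to 12) instead of 20. That is the only loss. No extra patients are needed, and the groups and doses stay as they are.

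**If staging is kept:** reconcile sections 2, 7, 8.2 and 8.4 so that they say the same thing:

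- Only timing is randomised, within each dose stage.
- The block size divides 20. For example, blocks of 4 give 20/4 = 5 blocks with 2 per timing group, hence exactly 10:10.
- The dose contrast is described as sequential and non-randomised, and the statement that the randomisation serves to inform dose is withdrawn.
- Both dose groups are assayed in the same LC-MS series where sample volume allows. This is conditional because only about 20 µL of perilymph is taken and no reserve is mentioned. It would remove assay-run differences but no other period effect.

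The first option costs a new list and an amendment of a few sentences. The second costs the text amendment, a list with the new block size, and coordination with the laboratory.

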## **8.3 Blinding**

No blinding is required in this study.

## **8.4 Benefit and risk assessment**

This study consists of a perilymph and a blood sample during cochlear implantation. Patients included in the study are deaf or profoundly hearing impaired. As previously shown in other studies sampling of the perilymph is a safe method.

This study can give us information on the absorption of Triamcinolone acetate by perilymph as well as information on the stability of Triamcinolone acetate after absorption of the perilymph. Since Triamcinolone acetate is used in the treatment of sudden SNHL and preoperatively, this study can deliver necessary information on the best timing of drug application and the necessary dose.

Additionally, a blood sample is taken, which can lead to known risks such as infections and hematoma.

## **8.5 Study procedures**

### **8.5.1 General rules for trial procedures**

- All study measures like blood sampling and measurements have to be documented with date (dd:mm:yyyy).
- In case several study procedures are scheduled at the same time point, there is no specific sequence that should be followed.

- The dates of all procedures should be according to the protocol. The time margins mentioned in the study flow chart are admissible. If for any reason, a study procedure is not performed within scheduled margins a protocol deviation should be noted, and the procedure should be performed as soon as possible or as adequate.
- If it is necessary for organizational reasons, it is admissible to perform procedures, which are scheduled for one visit at two different time points. Allowed time margins should thereby not be exceeded.

#### **8.5.2 Screening investigation**

Patients scheduled for cochlear implantation will be asked to participate in the study.

Inclusion and exclusion criteria will be evaluated at the end outpatient's department.

If patients fulfill inclusion and exclusion criteria and consent to the study is given a reevaluation on day 0 will be carried out. If the second evaluation has a positive outcome patients will then be included in the study on day 0.

#### **8.5.3 End-of-study (EOS) examination**

One week after surgery patients routinely are scheduled for wound examination and stitch removal as well as scheduling of cochlear implant fitting. During this examination adverse events will be evaluated. Additionally, ear microscopy is carried out.

## **9. SAFETY DEFINITIONS AND REPORTING REQUIREMENTS**

### **Adverse events (AEs)**

#### **9.1.1 Summary of known and potential risks of the study drug**

##### **Known side effects:**

##### **Cardiovascular**

Arrhythmia, heart failure

##### **Musculoskeletal**

Aseptic necrosis of femoral and humeral heads, loss of muscle mass, muscle weakness, osteoporosis, pathologic fracture of long bones, tendon rupture, and vertebral compression

fractures, bone mineral density loss and osteoporosis, steroid myopathy, vasculitis

### **Gastrointestinal**

Peptic ulcer with potential perforation and hemorrhage, perforation of small and large bowel, pancreatitis, abdominal distention and ulcerative esophagitis

### **Dermatologic**

Impaired wound healing, thin, fragile skin, petechiae and ecchymoses, facial erythema, increased sweating, and suppressed reactions to skin tests, purpura, striae rubrae, hyperpigmentation, steroidakne, allergic dermatitis

### **Nervous system**

Convulsions, increased intracranial pressure with papilledema, vertigo and headache, pseudotumor cerebri, manifestation of a latent epilepsie, sleeping disorders, neuritis, paresthesia

### **Endocrine**

Menstrual irregularities, postmenopausal vaginal bleeding, hirsutism, suppression of growth in children, manifestations of latent diabetes, increased requirements for insulin or oral hypoglycemic agents in diabetics, decreased carbohydrate tolerance, and secondary adrenocortical and pituitary unresponsiveness, impotence, pseudo-cushing syndrome, weight gain, negative protein and calcium balance, increased appetite

### **Ocular**

Cataract, glaucoma, increased intraocular pressure, glaucoma and exophthalmos, cornea perforation

### **Hypersensitivity**

Anaphylactoid reactions, anaphylaxis, and angioedema

### **Vascular diseases**

Necrotizing angiitis, higher risk of arteriosclerosis and thrombosis

### **Electrolyte dysbalance**

Sodium retention, water retention, higher potassium excretion, hypokalemic alkalosis,

hypertension, hyperglycemia, glukosuria

### **Other**

Anaphylactic reaction, feeling of heat

### **Medications with potential interactions:**

Cardiac glycosides

ACE inhibitors

Chloroquine, Hydrochloroquine, Mefloquine

Aspirin

NSAIDs

Oral Anticoagulants

Bupropion

Methotrexate

### **9.1.2 Definition of adverse events**

An AE is any untoward adverse change from the subject's baseline condition, i.e., any unfavorable and unintended sign including an abnormal laboratory finding, symptom or disease which is considered to be clinically relevant by the physician that occurs during the course of the study, whether or not considered related to the study drug.

Adverse events include:

- Exacerbation of a pre-existing disease.
- Increase in frequency or intensity of a pre-existing episodic disease or medical condition.
- Disease or medical condition detected or diagnosed after study drug administration even though it may have been present prior to the start of the study.
- Continuous persistent disease or symptoms present at baseline that worsen following the start of the study.
- Lack of efficacy in the acute treatment of a life-threatening disease.
- Events considered by the Investigator to be related to study-mandated procedures.
- Abnormal assessments, e.g., ECG and physical examination findings, must be reported as AEs if they represent a clinically significant finding that was not present at baseline or worsened during the course of the study.

- Laboratory test abnormalities must be reported as AEs if they represent a clinically significant finding, symptomatic or not, which was not present at baseline or worsened during the course of the study or led to dose reduction, interruption or permanent discontinuation of study drug.

Adverse events do not include:

- Pre-planned interventions or occurrence of endpoints specified in the study protocol are not considered AE's, if not defined otherwise (eg.as a result of overdose)
- Medical or surgical procedure, e.g., surgery, endoscopy, tooth extraction, transfusion. However, the event leading to the procedure is an AE. If this event is serious, the procedure must be described in the SAE narrative.
- Pre-existing disease or medical condition that does not worsen.
- Situations in which an adverse change did not occur, e.g., hospitalizations for cosmetic elective surgery or for social and/or convenience reasons.
- Overdose of either study drug or concomitant medication without any signs or symptoms. However, overdose must be mentioned in the Study Drug Log.

